### Statistical analysis plan

Normality of all data will be tested using Shapiro–Wilk’s test, based on which data will be appropriately described. Continuous variables will be reported as means ± standard deviation and noncontinuous variables will be reported as the median and interquartile range. Unpaired Student’s *t* test or Mann–Whitney U statistics will be used to compare the demographic variables and baseline outcomes between the two groups. Based on the data distribution of the study outcomes, grip strength, peg-board dexterity, applied dexterity and applied strength (Arthritis Hand Function Test items), DASH and number of exercise sessions completed in 6 weeks, changes over time (pre to post intervention) within each group will be assessed by paired Student *t* test or Wilcoxon signed-rank test. Differences in study outcomes between groups (control versus experimental) post intervention will be analyzed using unpaired Student *t* test or Mann–Whitney *U* test. An intention-to-treat analysis will be performed by including all the participants regardless of adherence to the study protocol. The last-observation-carried-forward method will be utilized to minimize the number of missing values due to dropouts. Statistical significance will be set at the *P* <0.05 level (two-tailed) for all analyses. The Consolidated Standards of Reporting Trials statement 2010 flow diagram will be used to explain the stages of the randomized controlled trial

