**Methods/Design:**

The ongoing study is a 6-week, single-center, parallel-group, equally allocated and assessor-blinded pilot randomized controlled trial. Thirty people with rheumatoid arthritis or osteoarthritis affecting the hand will be randomized to receive either conventional hand exercises or the task-oriented training. The purpose is to determine a preliminary estimation of therapeutic effectiveness and feasibility of the task-oriented training program. Performance based and self-reported hand function, and exercise compliance are the study outcomes. Changes in outcomes (pre to post intervention) within each group will be assessed by paired Student *t* test or Wilcoxon signed-rank test and between groups (control versus experimental) post intervention using unpaired Student *t* test or Mann–Whitney *U* test.

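### No outcome has one fixed between-group analysis: the observed distribution picks a t test or a rank test on post values, at about 15 per arm, in a pilot meant to estimate an effect

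*Protocol article*

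**What the plan says.** The Statistical analysis plan section begins: "Normality of all data will be tested using Shapiro–Wilk’s test", with the description of the data to follow from the result. The sentence after it sets the summary statistics by a different criterion, the type of variable: "Continuous variables will be reported as means ± standard deviation and noncontinuous variables will be reported as the median and interquartile range".

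The tests are then named in pairs. The within-group sentence begins "Based on the data distribution of the study outcomes, grip strength, peg-board dexterity, applied dexterity and applied strength", continues with the DASH and the number of sessions completed, and says that changes "within each group will be assessed by paired Student *t* test or Wilcoxon signed-rank test". The between-group sentence says that differences "post intervention will be analyzed using unpaired Student *t* test or Mann–Whitney *U* test".

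The abstract repeats both either/or choices. It also gives the aim of the trial: "The purpose is to determine a preliminary estimation of therapeutic effectiveness and feasibility of the task-oriented training program".

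**The concern.** The between-group comparison carries the first hypothesis, yet no outcome has a single analysis for it. Two analysts following the same text could report different tests for the same outcome, and neither would be departing from the plan.

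The two routes do not deliver the same thing. A t test goes with a difference in means. A Mann–Whitney test does not by itself give a difference on the outcome's own scale. If the sample decides the route, one Arthritis Hand Function Test item may be summarised as a mean difference and the next only as a rank comparison, for reasons owed partly to chance. The next trial would be planned from these estimates, so their scale should be known before the data are seen.

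Both routes also compare post-intervention values alone, although the same outcomes are measured at baseline.

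**Working it through.** The protocol gives no effect size, SD or power, so it has no figure to reproduce. The distribution shapes below are assumptions.

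**Inputs from the protocol.** Thirty participants (Sample size calculation) at 1:1 (Randomization) give 30 / 2 = 15 per arm. The two-sided level is 0.05 for all analyses. Six outcomes are listed: grip strength, peg-board dexterity, applied dexterity, applied strength, DASH and completed sessions. Peg-board and applied dexterity are times in seconds. Sessions are counted out of 24.

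**Step 1: how often Shapiro–Wilk rejects.** Simulation with 6,000 replicates per shape, test at 0.05:

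| Assumed shape | One arm, n=15 | Either arm | Pooled, n=30 |
|---|---|---|---|
| Normal | 5% | 10% | 5% |
| Lognormal, log-SD 0.25 | 15% | 27% | 27% |
| Gamma, shape 4 | 21% | 38% | 45% |
| Lognormal, log-SD 0.4 | 28% | 48% | 56% |
| Lognormal, log-SD 0.5 | 38% | 63% | 72% |
| Session count capped at 24 | 49% | 74% | 90% |
| Lognormal, log-SD 1 | 83% | 97% | 99% |

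A separate run at log-SD 0.3 / 0.5 / 0.7 gave 18% / 38% / 60% per arm. Under moderate skew, the test therefore misses the departure in most single arms.

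**Step 2: does the unstated unit matter?** Yes. Gamma (shape 4) data go to the rank test 21% of the time if one arm is checked and 45% if the arms are pooled. If each arm is checked, the chance of opposite verdicts is 2p(1−p):
- p = 0.18: 2 × 0.18 × 0.82 = 0.30
- p = 0.38: 2 × 0.38 × 0.62 = 0.47
- p = 0.60: 2 × 0.60 × 0.40 = 0.48

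Simulation gave 30% / 46% / 48%. At log-SD 0.5, checking post values and checking pre–post differences gave different verdicts in about 37–40% of samples (assumed pre–post correlations 0.6 and 0.9).

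**Step 3: mixing of routes by chance alone.** If all six outcomes were truly normal and independent, the chance that at least one goes to a rank test is 1 − 0.95^6 = 26% with one check each, or 1 − 0.95^12 = 46% with both arms checked.

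**Step 4: type I error.** Across the assumed shapes at 15 per arm:
- t test fixed in advance: 3.8–5.3%
- Mann–Whitney fixed in advance: 4.2–4.9%
- two-stage rule, either arm rejecting: 4.5–5.9%
- two-stage rule, pooled check: 4.4–5.4%

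The Monte Carlo standard error near 5% is √(0.05 × 0.95 / 6000) = 0.3 points. Fixing the test moves the error rate by about 1 point at most.

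**Step 5: what a baseline-adjusted estimate would gain.** Against post values alone, the variance ratio is about (1 − ρ²) × (1 + 1/(N − 4)), with N = 30 and ρ the pre–post correlation (assumed 0.5–0.8):
- ρ = 0.5: 0.75 × 27/26 = 0.78, a reduction of about 22%
- ρ = 0.8: 0.36 × 27/26 = 0.37, a reduction of about 63%

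**The case against.** Several stronger readings are tempting, and the protocol does not support them.

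- **That the pre-test is close to a coin toss.** This holds only for moderate skew or capped counts. Per-arm rejection runs from 5% to 83% over the assumed shapes, and the protocol gives no distributions.
- **That the wrong quantity is checked, or that each arm is checked separately.** The text refers only to all data. That excludes neither differences nor pooling, and a pooled check cannot produce conflicting arms. The point that stands is that the unit is unstated and that it changes the route.
- **That Shapiro–Wilk is expressly the selector.** It is tied in words only to description, and "Based on the data distribution of the study outcomes" introduces the within-group tests. Its role in the between-group choice is the natural reading, supported by the abstract's either/or, but it is an inference.
- **That error rates are inflated.** Among trials in which both arms pass the check, the t test's error is about 7–8% at log-SD 0.5 and 9–10% at 0.7. Such trials are only about 0.62² = 38% and 0.40² = 16% of the total. These conditional rates are not the error rate of the procedure.
- **That the effect estimate is lost.** If continuous variables are always given as mean and SD, an unadjusted mean difference and interval can be worked out whichever test was used. It would, however, stand beside a P value from another method. That reporting sentence also sits awkwardly with the normality-based one before it.

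A published article may also leave an effect measure, interval or unit of checking to a fuller plan, so their absence is not itself the criticism. The criticism is of the rule that is stated: paired alternatives for every outcome, chosen from the data. With 30 participants and no formal sample size calculation, this is a moderate weakness, not a fatal one.

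**Conclusion.** The point holds as a weakness in pre-specification and estimation. No outcome, including the primary, has one fixed between-group analysis, and the stated rule lets the sample choose between a t test and a rank test on post values. At about 15 per arm the choice is unreliable under moderate skew: about 18–38% detection per arm for lognormal data with log-SD 0.3–0.5. That degree of skew is assumed; it is plausible for the timed items but not documented. The overall false-positive rate stays at about 5–6%. What suffers is the pilot's ability to give an estimate for every outcome on a scale set in advance. The plan also forgoes a more precise baseline-adjusted estimate that the collected data would support. The change should be made, but the trial's validity does not turn on it.

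**What to change.** Remove normality testing as the selector of the test, and pre-specify the following.

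1. **Each Arthritis Hand Function Test item and the DASH:** a linear model of the post value on arm and baseline value, plus diagnosis (RA or OA) if randomization is in fact stratified by it; the protocol makes that conditional on recruitment. Name the log scale in advance for peg-board and applied dexterity. Report the adjusted difference, or the ratio for the log-scale items, with a 95% CI.
2. **Completed sessions:** these have no baseline and are capped at 24, so the model above does not apply. Report an unadjusted between-group difference with a 95% CI by one pre-named method, such as a bootstrap or permutation interval.
3. **Sensitivity:** one pre-named rank or permutation test, run whatever the data look like. It may still disagree with the main analysis, but the main analysis will have been fixed beforehand.

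The cost is analysis-plan wording, with no new data or visits. The small downside is that a pre-set scale may fit an outcome poorly, which the fixed sensitivity analysis covers.

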### Hypotheses

The first hypothesis is that the experimental group receiving task-oriented training will show greater improvements in performance-based, self-reported hand function and reduction in pain and stiffness levels as compared with the control group receiving conventional hand exercises.

The second hypothesis is that the task-oriented training will be feasible in terms of compliance and treatment safety and will demonstrate better completion rate as compared with conventional hand exercises.

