### Outcome measures

#### Primary outcome measure

The primary outcome measure will be the Arthritis Hand Function Test, an 11-item performance-based test that measures grip and pinch strength, dexterity, applied strength and dexterity in people with arthritis. Test–retest reliability of the Arthritis Hand Function Test measured by the intraclass correlation coefficient in 20 individuals with RA ranged from 0.53 to 0.96; inter-rater reliability ranged from 0.89 to 1.0. Test–retest reliability in 26 individuals with OA ranged from 0.7 to 0.96; inter-rater reliability ranged from 0.99 to 1.0 [38,39].

The peg-board dexterity test measures the time taken in seconds to place and remove nine pegs into the nine holes. Applied dexterity is the total time taken (seconds) to complete the following tasks: lacing a shoe, tying a bow, fastening/unfastening four buttons, fastening/unfastening two safety pins, cutting putty with a knife and fork, and manipulating coins into a slot.

Applied strength will be measured by the total number of soup cans lifted in a tray and the volume (ml) of water lifted in a pitcher.

Grip strength of the dominant hand will be clinically tested using a handheld dynamometer (Biometrics isometric hand dynamometer G100; Biometrics Ltd, Cwmfelingach, Gwent, UK). Grip strength will be recorded in kilograms and the best score out of the three consecutive trials will be used for analyses. Similarly, three-point pinch strength will be measured using a pinch meter (Biometrics precision pinch meter P200; Biometrics Ltd).

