### Baseline visit

An initial assessment will be conducted during the first visit, which will include the following: documentation of demographic information such as age, sex, occupation, diagnosis and disease duration; documentation of individual specific problems during specific tasks of daily living; observation of fine/gross finger abilities on handling different objects of daily life; and assessment of primary and secondary study outcomes.

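### The arms are compared on unadjusted week-6 values and change is tested only within each arm, so improvement is not compared directly and collected baseline values are left out of the treatment comparison

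*Protocol article*

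**What the plan says.** The first hypothesis, under Hypotheses in the protocol article, is comparative and is about change: "will show greater improvements in performance-based, self-reported hand function and reduction in pain and stiffness levels as compared with the control group".

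The Statistical analysis plan section names two analyses of the outcomes:

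- Inside each arm: "changes over time (pre to post intervention) within each group will be assessed by paired Student" t test or a Wilcoxon signed-rank test.
- Between arms: "Differences in study outcomes between groups (control versus experimental) post intervention will be analyzed using unpaired Student" t test or a Mann–Whitney test.

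Both are judged at two-sided P<0.05. The abstract's Methods/Design paragraph gives the same pair in one sentence: "Changes in outcomes (pre to post intervention) within each group will be assessed by paired Student" t test or its rank counterpart, "and between groups (control versus experimental) post intervention using unpaired Student" t test or its rank counterpart. Neither place names a baseline covariate, a diagnosis term or a between-arm comparison of change.

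The Baseline visit section includes "assessment of primary and secondary study outcomes", and the Randomization section places allocation after that visit. Baseline values of the Arthritis Hand Function Test and DASH will therefore exist before allocation.

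**The concern.** The stated aim is a preliminary estimate of effectiveness, so the quality of the between-arm estimate is what matters. Two things in the plan work against it.

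First, the treatment comparison ignores where participants started. With 15 per arm, the arms will often differ by chance at baseline, and part of that difference carries into the week-6 comparison. The plan tests for baseline differences but attaches no action to the result.

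Second, the only analysis of improvement is done separately in each arm. A before–after test in one arm mixes any treatment effect with retest learning and natural course. Finding one arm significant and the other not is no evidence that the arms differ. Because these tests share the significance level of the between-arm test, nothing in the plan marks them as descriptive.

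**Working it through.** **Inputs from the protocol article.** 30 participants, allocated 1:1, so 15 per arm (Sample size calculation; Randomization). Two-sided 5% level (Statistical analysis plan). One post-baseline assessment, at the end of week 6. No effect size, SD or power is stated, so there is no planned figure to reproduce.

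**Assumptions.** Outcome SD of 1 at both visits. Correlation r between baseline and week 6 of 0.3, 0.5, 0.7 or 0.8; the article does not give it. The Primary outcome measure section quotes test–retest coefficients for the Arthritis Hand Function Test ("in 20 individuals with RA ranged from 0.53 to 0.96"; 0.7 to 0.96 in OA). These are only a guide: they are not six-week correlations under treatment and they say nothing about DASH.

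**1. Does the planned test aim at the right quantity?** Under randomization the expected baseline means are equal, so the expected week-6 difference equals the expected difference in change. A simulation of 20,000 trials at each of r = 0.5, 0.7 and 0.9, with a true effect of 0.8 SD, gave a mean estimate of about 0.80 for the week-6 comparison, the change-score comparison and ANCOVA alike. With no effect, each rejected in about 5% of trials. The planned test is valid; what differs is precision.

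**2. Chance imbalance.** SD of the baseline difference = √(2/15) = 0.365. P(|difference| > 0.5 SD) = 2[1 − Φ(0.5/0.365)] = 2[1 − Φ(1.37)] = 0.17. An imbalance of 0.5 SD shifts the unadjusted week-6 estimate by r × 0.5, that is 0.15, 0.25, 0.35 or 0.40 SD at the four values of r. ANCOVA removes this shift.

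**3. Detectable difference, 80% power.** The standard error is √(2v/15).

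- Unadjusted: v = 1, 28 df. The noncentral t distribution requires 2.902 standard errors, so 2.902 × 0.365 = 1.06 SD.
- Adjusted for baseline and diagnosis: v = (1 − r²)(1 + 2/24), 26 df, requiring 2.910 standard errors. Diagnosis is assumed to explain nothing beyond baseline, so it only costs a degree of freedom. The factor 1 + 2/24 = 1.083 is an approximate small-sample penalty; 1 + 2/25 would change the results by less than 0.002 SD.

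| r | 1 − r² | standard error | detectable difference (SD) |
|---|---|---|---|
| unadjusted | – | 0.365 | 1.06 |
| 0.3 | 0.91 | 0.363 | 1.06 |
| 0.5 | 0.75 | 0.329 | 0.96 |
| 0.7 | 0.51 | 0.271 | 0.79 |
| 0.8 | 0.36 | 0.228 | 0.66 |

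The 95% CI half-width is 2.048 × 0.365 = 0.75 SD unadjusted, and 2.056 × 0.271 = 0.56 SD at r = 0.7.

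**4. Why not compare change scores?** Their variance factor is 2(1 − r): 1.4, 1.0, 0.6 and 0.4. At r = 0.3 this is worse than ignoring baseline (power 43% against 56% for a true difference of 0.8 SD). ANCOVA avoids that loss.

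**5. Within-arm tests when both arms improve equally.** Let p be the power of a paired t test with n = 15 at standardized change dz. The chance that exactly one arm is significant is 2p(1 − p).

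| dz | p | 2p(1 − p) |
|---|---|---|
| 0.2 | 0.112 | 20% |
| 0.5 | 0.438 | 49% |
| 0.6 | 0.580 | 49% |
| 0.8 | 0.821 | 29% |
| 1.0 | 0.949 | 10% |

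**The case against.** A reader might infer that the first hypothesis is never tested. The documents do not support that. Outcomes are measured before randomization, so the week-6 comparison estimates the same effect as a comparison of change (step 1). The abstract, whose sentence opens with changes in outcomes, can even be read loosely as comparing changes, although it too specifies post intervention.

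A reader might also infer that the baseline data are wasted. They are not: they feed the within-arm tests and the between-arm baseline comparison. They are missing only from the treatment comparison.

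Nor does every outcome have a baseline. The number of exercise sessions completed is a listed outcome with no value before the intervention, so ANCOVA on baseline cannot apply to it and the planned unadjusted comparison is the workable one.

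The size of the gain can fairly be challenged. It depends on an assumed r and disappears at r = 0.3. A low r is possible for DASH, because entry is restricted to scores of 25 to 50. The 49% figure is close to the 50% maximum that 2p(1 − p) can reach, and the chance is much lower for very small or large changes. Stratification by RA or OA is conditional on recruitment numbers, so the design does not clearly require a diagnosis term.

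Finally, this is a 30-person pilot with no powered hypothesis, and a between-arm test is prespecified. All of this stands and limits the severity. It does not remove the point: the method is stated, a better one uses data already collected, and precision serves the pilot's own aim of estimation.

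**Conclusion.** The point holds as one of efficiency and interpretation, not of validity. Improvement is not compared directly between arms, and baseline values are unused in the treatment comparison. At 15 per arm, a baseline imbalance above 0.5 SD is left uncorrected in 17% of trials. The detectable difference would move from 1.06 SD to between about 1.06 SD (r = 0.3) and 0.66 SD (r = 0.8). The within-arm tests can split significant from non-significant in about 10–49% of trials even when both arms improve equally.

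These figures assume normal outcomes with equal SDs, complete data on 15 per arm, and the stated range of r. The benefit is likely to differ by outcome and may be negligible for DASH. This should be fixed; it is not a reason to regard the planned between-arm test as invalid.

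**What to change.** - For each outcome with a baseline value (the Arthritis Hand Function Test items and DASH), make the between-arm analysis an ANCOVA of the week-6 value on arm and baseline value. Add RA/OA if randomization is stratified by it. Report the adjusted difference with its 95% CI.
- Keep the unadjusted between-arm comparison for the number of sessions completed.
- Report within-arm changes descriptively, without significance tests.
- Make the abstract and the Statistical analysis plan section say the same thing.

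The cost is one or two degrees of freedom and a change of analysis wording. No new data, visits or participants are needed.

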### Randomization

After the baseline assessment, participants will be randomly allocated into one of the two groups. The randomization procedure will be as follows: sequence generation, the two groups will be generated with equal allocation ratio (1:1) by referring to a computer-generated group allocation –randomization will also be stratified, RA or OA condition wise, depending upon the number of participants being recruited; allocation concealment, allocation will be concealed in sequentially numbered, opaque, sealed envelopes and will be opened only after the participant details are written on the envelope; implementation, a staff member who is not involved with the trial will generate the random numbers, do the allocation concealment and keep them until the end of the study; and blinding, an independent assessor blinded to the group allocations will evaluate the study outcomes at baseline and at the end of the sixth week.

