### Six-week home program

After the training sessions, both groups will be provided with a written protocol of their home program. The protocol will include clear description of each exercise/manipulation to be performed, number of repetitions (control group) or minutes of play (experimental group) and the number of sessions per week.

The control group will perform the conventional hand exercise program, and the experimental group will perform the task-oriented training with personalized objects, selected by the clinical judgment drawn from the baseline findings.

At the start of the home program, the study staff will attend each participant’s home to ensure proper set-up of their respective intervention. A week later, both groups will be contacted through telephone calls or electronic mails to assess their ability to manage the home program. Both groups will be asked to perform their exercises four times per week for 6 weeks. The pain and stiffness files can be saved to a USB flash drive or sent as an email attachment for regular monitoring by the study staff.

Treatment progression or modification will be made for both groups every 2 weeks depending on individual needs and abilities. When no increased symptoms (assuming a benchmark score >5 in the pain and the stiffness scales) are reported during or after exercises, progression will be followed as in Table 1. In cases of any symptoms being reported, the treatment parameters will be modified by reducing the number of repetitions or minutes of play. Any occurrence of increased pain or stiffness continuing over 1 week would be recorded as an adverse event. The intervention will be discontinued and the participant will be referred to his/her general practitioner.

**Table 1 T1:** Treatment progression guidelines for both groups

**Group**	**Progression goals**	**0 to 2 weeks**	**3 to 4 weeks**	**5 to 6 weeks**
Control group	Number of repetitions of each exercise	5	8	12
Experimental group	Personalized objects	3 to 4	4 to 5	5 to 6
Both groups	Strengthening (60 to 70% of one repetition maximum	1 set ×10 repetitions	1 set ×15 repetitions	1 set ×20 repetitions
Both groups	Exercise duration	15 minutes	20 minutes	25 minutes

The study staff providing the interventions will maintain a record of treatment sessions, exercises prescribed and their progression for each participant. Information on adverse symptoms would include severity, duration and the appropriate treatment modifications done.

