A final session to evaluate the primary and secondary study outcomes will be conducted at the end of the 6th week of the home program.

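### With assessments only at baseline and week 6, last observation carried forward fills every missing hand function test and DASH result with zero change, which biases the comparison if participants improve and completion differs between arms

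*Protocol article*

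**What the plan says.** The Statistical analysis plan section fixes the handling of missing data: "The last-observation-carried-forward method will be utilized to minimize the number of missing values due to dropouts". It sets this inside an analysis of everyone randomised: "An intention-to-treat analysis will be performed by including all the participants regardless of adherence to the study protocol". The between-arm test uses follow-up values: "Differences in study outcomes between groups (control versus experimental) post intervention will be analyzed using unpaired Student *t* test", or the Mann–Whitney test.

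The schedule has two assessment points. Under Randomization, "an independent assessor blinded to the group allocations will evaluate the study outcomes at baseline and at the end of the sixth week". The text that closes the home-programme description confirms a single follow-up visit: "A final session to evaluate the primary and secondary study outcomes will be conducted at the end of the 6th week of the home program".

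Three other statements bear on the point. The second hypothesis is that task-oriented training "will demonstrate better completion rate as compared with conventional hand exercises". The Background expects graded mobility exercises to improve hand function. Under Six-week home program, when increased pain or stiffness lasts more than a week, "The intervention will be discontinued and the participant will be referred to his/her general practitioner".

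**The concern.** Carrying the last observation forward presupposes at least one assessment between baseline and the endpoint. Here there is none for the primary outcome or the DASH, so the rule amounts to baseline carried forward. Each missing week-6 result enters the analysis as a participant who did not change, and it is treated as if it had been measured.

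This matters because the protocol's own expectations supply the two conditions for bias. It expects exercise to improve function, and it hypothesises better completion in the experimental arm. If both hold, the control arm receives more imputed zeros, and a difference in completion (second hypothesis) leaks into the estimate of efficacy (first hypothesis). If dropout is equal, the imputed zeros pull a real difference towards zero. The trial exists to give a preliminary estimate of effectiveness, so the distortion falls on its main product.

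The number of sessions completed, which the analysis section lists among the outcomes, has a simpler problem: it is a count over the six weeks with no baseline value, so there is nothing to carry forward.

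**Working it through.** **Inputs from the protocol.** Thirty participants allocated 1:1, hence 15 per arm. Assessments at baseline and week 6. Unpaired test on follow-up values, two-sided 5% level. The protocol states no dropout rate, expected improvement or SD, and no formal sample size calculation, so there is no figure of its own to reproduce.

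**Assumptions.** Effects are in SD units, with baseline and week-6 SD both 1 and a correlation of 0.7 between them. Dropout is unrelated to outcome, so dropouts would have improved on average as much as completers in their arm. Improvement and dropout values are illustrative.

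**Closed form.** Let D_E and D_C be the true mean improvements, and dE and dC the dropout proportions. Each dropout contributes zero change, so

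expected difference = D_E(1 − dE) − D_C(1 − dC).

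Baseline means are equal in expectation under randomisation, so this holds for follow-up values as well as for change. With equal true improvement D in both arms it reduces to D × (dC − dE).

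**No true difference, dropout 2/15 experimental and 5/15 control:**
- D = 0.6: 0.6 × (5/15 − 2/15) = 0.6 × 0.2 = 0.12 SD.
- D = 0.8: 0.8 × 0.2 = 0.16 SD.
- D = 0: no bias at any dropout split.
- Dropout reversed (5/15 experimental, 2/15 control), D = 0.6: −0.12 SD, against the experimental arm.

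Simulation of 40,000 trials agrees with these differences. The unpaired t test on follow-up values rejects in about 5.2 to 5.8% of trials in the first two cases, against about 5% when only observed values are used.

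**True difference 0.50 SD (0.8 versus 0.3), dropout 3/15 in each arm:** 0.8 × 0.8 − 0.3 × 0.8 = 0.64 − 0.24 = 0.40 SD, a loss of one fifth. Simulated power is about 17%. Analysing the observed 12 versus 12 gives about 21 to 22% and an unbiased 0.50 SD.

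**More extreme case, no true difference:** D = 1.0 with dropout 1/15 versus 7/15 gives 1.0 × 6/15 = 0.40 SD, with type I error of about 15%.

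**On the DASH scale:** an assumed 10-point improvement in both arms and three more dropouts among controls gives 10 × 3/15 = 2.0 points of false difference. For assumed improvements of 5 to 15 points the range is 1.0 to 3.0.

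**When dropouts truly return to baseline:** with completers improving by 0.5 SD and dropout 1/15 versus 4/15, the carried-forward difference and the true difference are both about 0.10 SD, so there is no bias.

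**The case against.** The strongest defence is that zero change may be near the truth for someone who abandons a six-week exercise programme. If so, the rule does little harm. That stands as a condition on the finding: the bias requires that dropouts would on average have changed. A reader might infer that any imbalance in completion turns into a spurious effect, and the formula shows that it does not.

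Second, better completion in the experimental arm is a hypothesis under test, not a known rate. The opposite pattern would bias against that arm. This also stands.

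Third, the numerical effect is modest. At 2/15 versus 5/15 the bias of 0.12 SD compares with a sampling SD of about 0.37 SD for the estimated difference. The type I error barely moves, and the total error (root mean square) of the carried-forward estimate is no worse than that of the observed values, about 0.38 versus 0.42 SD. A reader might expect false precision as well, but the calculations do not show it. The harm is systematic error in the estimate.

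Fourth, one might infer that participants stopped for prolonged symptoms are automatically filled with baseline, hiding their worsening. The protocol stops the intervention for them; it does not say that they miss the week-6 session. Pain and stiffness are also rated at home before and after each session, and adverse symptoms are recorded separately, so the carry-forward problem described here does not extend to those home ratings.

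Finally, this is a small pilot that will report completion and a participant flow diagram, so unequal dropout would be visible. That lowers the severity, but it does not correct the estimate.

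**Conclusion.** The point holds in a conditional form and should be fixed. For the hand function test items and the DASH, the stated rule imputes exactly zero change for anyone without a week-6 value. If participants would have improved and completion differs, the comparison is biased by D × (dC − dE), towards the experimental arm if the protocol's completion hypothesis is right.

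Under the moderate assumptions above this is about 0.12 to 0.16 SD with little effect on the false-positive rate. Equal 20% dropout shrinks a true 0.50 SD to 0.40 SD. These sizes rest on assumed improvement and dropout, and on dropouts resembling completers. They go to zero if mean change is nil or if dropouts truly stay at baseline. Separately, the rule cannot be applied to the session count at all.

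**What to change.** Replace last observation carried forward as the primary missing-data rule:

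1. State that participants who stop the intervention are still invited to the week-6 assessment already scheduled.
2. Analyse all randomised participants with an observed week-6 value, in their assigned arm, adjusting for the baseline value of the outcome.
3. Tabulate missing week-6 data by arm and reason, and show baseline carried forward only as a sensitivity analysis, under that name.
4. Say that no carry-forward applies to the number of sessions completed.

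The trial is described as ongoing, so this needs only a change of analysis wording and one instruction about attendance at an existing visit. The cost is fewer analysed values and a slightly wider interval. The observed-value analysis is itself unbiased only if missingness is ignorable given baseline, which is why the sensitivity analysis and the table of reasons belong beside it.
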